**Fig. 1 Fig1:**
[figure not shown]
Trial flow chart

### Setting

We aim to recruit 175 SystmOne GP practices from all 15 UK CRN’s. The Clinical Research Network (CRN) invite research active SystmOne GP practices to express an interest in taking part in the study.

### GP practice set-up

Interested practices are sent a local document pack by the study team and practices are asked to return a set of documents including a CV, Good Clinical Practice (GCP) certificates and a signed site contract. Sites undergo remote training in trial conduct and the use of the TRANSFoRm electronic platform.

A site is only greenlighted once all local documents have been completed and the principal investigator (PI) has completed the online training. At this point the TRANSFoRm electronic platform is installed onto the PI’s computer. Once a site is greenlighted, additional clinicians from that practice can complete the REST training package, be added to the site delegation log and the TRANSFoRm platform can be downloaded onto additional practice computers.

### Participants and eligibility

Eligible participants are children aged ≥ 12 months to < 16 years whose parents/legal guardians are seeking primary medical care for acute-onset unilateral otorrhoea as the presenting symptom of recent-onset (≤ 7 days) AOM. Detailed inclusion and exclusion criteria are detailed in Table 1.

**Table 1 Tab1:** Inclusion and exclusion criteria

Patient selection criteria	
**Inclusion criteria (child must meet all criteria):**	1. Children aged ≥ 12 months to < 16 years 2. Presenting with recent-onset (≤ 7 days) unilateral AOM with recent-onset (≤ 7 days) otorrhoea currently visible (or seen by parent/legal guardian ≤ 24 h) 3. Child attending with parent/legal guardian who is legally able to give consent in person 4. Parent/legal guardian willing and able to administer eardrops 5. Parent/legal guardian willing, able and available to complete the daily SRQ and received regular telephone calls from the study team
**Exclusion criteria (excluded if child meets any criterion at the time of entry):**	1. Symptoms/signs suggestive of bilateral AOM/AOMd 2. Child has symptoms/signs suggestive of serious illness and/or complications, e.g. mastoiditis and/or requires immediate hospitalisation 3. Child requires immediate orally administered antibiotics (e.g. for another infection or AOMd considered severe) 4. As per NICE guidelines [12], a child at high risk of serious complications: • Significant immunosuppression • Heart, lung, renal, liver or neuromuscular disease (defined as requiring ongoing inpatient or outpatient care from specialist teams) co-morbidities • Trisomy 21 (Down’s syndrome), cystic fibrosis or craniofacial malformation, such as cleft palate (these children are known to be at higher risk of AOM) 5. Grommet (ventilation tube) in situ in the ear with otorrhoea 6. Currently taking orally (for a respiratory tract infection) or topically administered (in the affected ear) antibiotics 7. Allergy to ciprofloxacin 8. Allergy to penicillin/anaphylaxis to another beta-lactam agent and allergy to clarithromycin 9. Child has taken part in any research involving medicines within the last 90 days 10. Child has already participated in this trial

*AOM* acute otitis media, *SRQ* Standard Recovery Questionnaire

### Patient screening and recruitment

The process of patient screening and recruitment is detailed below:
Children aged ≥ 12 months to < 16 years accompanied by a parent/legal guardian present to their GP with suspected AOMdGP invites parent and child to participate in the REST study and provides a parent information leaflet (child information leaflet for children over 6 years old)GP seeks verbal agreement from parents and assesses the child for eligibility using the TRANSFoRm electronic platformInformed consent/assent is sought from parents of eligible children, baseline data and contact details are collected via the TRANSFoRm platformChild is randomised using the TRANSFoRm platform and, if allocated, the drops or immediate antibiotics on an FP10 prescription (Standard UK prescription) are issued.

### Randomisation

After confirming eligibility and obtaining informed consent, participants will be randomised (stratified by age) to either (1) immediate topically administered ciprofloxacin 0.3% drops with (2) delayed orally administered antibiotics or (3) immediate orally administered antibiotics.

The randomisation sequence is generated by the Bristol Randomised Trials Collaboration (BRTC) and supplied to the TRANSFoRm electronic platform to be allocated to each successive participant recruited. A system for checking the correct randomisation allocation is built in to the TRANSFoRm platform. Clinicians will not be able to determine treatment allocation pre-randomisation.

### Consent

Parent Information Sheets (Additional file 2) will be given to the parents of potentially eligible children and discussed before consent is sought. Informed consent will be obtained from the parent or legal guardian of each child. Assent will be obtained from all children over the age of 6 years. Parents will also be given be the opportunity to consent to stool-sample collections (with the additional option of the sample being retained for future research in microbial infections), declining to consent to this element of the study will not exclude participation from other elements of the study. Parents will also be given the opportunity to consent to information being collected about their child being used to support other research in the future, and to this being shared anonymously with other researchers.

### Withdrawal

Participants remain in the trial unless they choose to withdraw, or if they are unable to continue. Parents can choose to completely withdraw their child or to withdraw from specific elements of the study without giving a reason. Any data collected up until this point will be retained for analysis. Information regarding the withdrawal criteria is detailed in the parent information leaflet.

### Interventions

#### Choice of comparator

We selected ciprofloxacin 0.3% drops as our topically administered antibiotic because it:
Is active against all common otopathogens [2]Is non-ototoxicIs widely and routinely available in the UKIs colourless so will not interfere with assessing otorrhoeaWill provide complementary evidence to the ZonMw-funded trial, which is using an antibiotic-steroid combination

We decided to avoid aminoglycoside drops because of concerns about potential ototoxicity. We have proposed delayed orally administered antibiotics as the second intervention since our previous trials [1, 20, 21] have achieved significant reductions in orally administered antibiotic consumption compared with immediate antibiotic prescribing (and similar symptom relief). Immediate orally administered amoxicillin (clarithromycin if allergic to penicillin) is the comparator as it reflects usual care and is well-tolerated.

#### Intervention description

Arm 1: (control) current usual care – orally administered amoxicillin suspension three times daily for 7 days (or orally administered clarithromycin twice daily for 7 days if allergic to penicillin).

Arm 2: (intervention) antibiotic drops, to be instilled three times daily into the discharging ear. Parents will be given written advice regarding how to administer the drops. This will include: (1) cleaning the outer ear of discharge that can be easily removed with a tissue; (2) tilting the child’s head to one side (to approximately 90°) when applying the eardrops; and (3) maintaining the tilt for a few minutes to improve penetration of the drops.

Arm 3:(intervention) a ‘delayed’ prescription for orally administered amoxicillin suspension antibiotics three times daily for 7 days (or orally administered clarithromycin twice daily for 7 days if allergic to penicillin). Parents will be given written advice to delay the prescription will consist of: (1) advising that the prescription is only ‘dispensed’ at a pharmacy if symptoms worsen or are not starting to improve by 4 days; and (2) safety-netting advice regarding the symptoms that should prompt review consultation (increasing pain, high temperatures, headaches, irritability or reduced feeding).

All groups will also receive standard advice to complete the antibiotic course and how to manage pain, fever and other symptoms (e.g. use of paracetamol/ibuprofen).

#### Post-trial care

Following participation in the study, children are returned to usual care by their GP. All participants will receive a summary of the results of the trial.

### Outcome measures

The primary outcome measure is time to resolution of the following symptoms: pain, fever, being unwell, sleep disturbance, otorrhoea and episodes of distress. The primary outcome is the time until all symptoms are rated by parents as ‘no’ or ‘very slight’ problem. This will be recorded by parents in the Symptom Recovery Questionnaire (SRQ).

Secondary outcome measures:
Duration of ‘moderately bad or worse’ symptoms (pain, fever, being unwell, sleep disturbance, otorrhoea; episodes of distress/cryingAppetite and interference with normal activities up to 14 daysAntibiotic and analgesic useAdverse events – diarrhoea, rash, vomiting, serious complicationsTreatment adherenceParent/legal guardian satisfaction with treatmentNHS resource use at 14 daysRepeat AOM and AOMd episodes, serious complications and the OM6 hearing questionnaire at 3 months;Qualitative evaluation of recruitment, medication satisfaction, adherence and follow-upAnalysis of stool sample to assess burden of resistance

### Assessment and follow-up

The components and timing of follow-up measures are shown in Fig. 2.

**Fig. 2 Fig2:**
[figure not shown]
Participant recruitment and follow-up timeline. *****Completed daily from day 1 to day 14

#### Clinician-recorded outcomes: baseline data collection form and contact form

During the consultation, clinicians will complete a baseline data collection form and contact detail form for all eligible participants. The baseline data collected includes acute clinical data and any relevant medical history relating to AOMd incidence.

A contact details form will record information from the parent/legal guardian including name, address, telephone number and availability to take calls from the research nurse.

#### Patient-reported outcomes

All parents/legal guardians are asked to complete a daily SRQ recording the symptoms identified by parents/legal guardians as important. The SRQ will be provided in electronic format via the TRANSFoRm app or in a paper version. The SRQ will provide a daily record of symptom burden and will be completed up to 14 days. The primary outcome will be collected using the SRQ with research nurse telephone calls on days 1, 3, 7, 10 and 14.

On day-7 and day-14 telephone calls, information on the use of healthcare resources including information about primary care contacts, use of 111, walk-in centres and hospital services will be obtained.

At month 3, use of hospital services will be collected by review of the patients’ EHR.

The final questionnaire will be sent 3 months after randomisation either electronically (web or iOS/Android app) via the TRANSFoRm platform or paper questionnaire. The questionnaire will ask about parent/legal guardian-reported hearing loss at 3 months as measured using the OM6 [22] questionnaire.

#### Storage and analysis of microbiological clinical samples

Plans for the collection, storage and evaluation of biological specimens can be found in Additional file 3.

### Economic data collection

The economic evaluation will explore the relationship between cost and outcomes for the three proposed methods of treating AOMd. This will be done for the short term (14 days) to assess the cost-effectiveness of immediate topically or delayed orally administered antibiotics compared with immediate orally administered antibiotics, and the longer term (3 months) in order to capture the effects of any recurrence of symptoms and lasting side effects. The perspectives will be from the NHS, parents/carers, and lost productivity due to time off work and school.

During the trial, participants will complete a symptom diary which will record any use of healthcare resources not available from the GP notes (for example, community care and the use of 111 and walk-in centres) and non-healthcare costs incurred by parents/carers during the first 14 days such as travel costs, purchase of over-the-counter medications, childcare and loss of earnings due to time off work. We will also ask about time off nursery/school.

### Qualitative data collection

The qualitative evaluation will explore the views and experiences of the trial processes, the acceptability of the different treatment options, and the barriers and facilitators to their use within, and future uptake outside the trial.

Purposive sampling [23] will select participants in order to capture maximum variation in views and experiences of a range of parents and primary care professionals. From parents who agree to trial participation and the interview, a purposive sample will be drawn in relation to site, arm of the trial, and socio-demographic variables such as socio-economic status. Parents who decline trial participation will also be invited to be interviewed. Primary care professionals involved in trial processes will also be purposively sampled in relation to site. Sample sizes will be determined by data saturation [23], such that no new themes are emerging from the data by the end of data collection. We anticipate including up to 20 clinicians, 20 participant parent interviews and 15 parent decliner/withdrawal telephone interviews.

In-depth interviews will be conducted with participating parents (from all arms of the trial) 14 days after randomisation [24]. Interviews with parents who declined to participate will be conducted within 7 of declining. These will be conducted by telephone at a time of the participant’s choosing. Interviews with primary care professionals will be conducted after 3–6 months of involvement in the trial to try to capture those with experience of recruitment. A flexible topic guide will be devised to ensure that the primary issues are covered across all interviews, but it will incorporate considerable flexibility to enable participants to introduce unanticipated issues, and they will be modified to reflect findings as they emerge. The researcher will use open-ended questioning techniques to elicit participants’ experiences and views of key events and participants will be asked to provide examples. Primary care professional’s interviews are expected to last around 30–45 min, parent interviews 30–40 min and those with parents who decline trial participation 10–20 min. Interviews will be recorded using a digital voice recorder, transcribed and anonymised to protect confidentiality.

### Trial oversight

The study is overseen by a Trial Management Group that meet on a monthly basis and consist of the chief investigator (CI), grant holders, study sponsor and any other staff responsible for the delivery of the trial. The Trial Steering Committee (TSC) provides independent supervision of the trial and oversees trial progress. The TSC consists of an independent chair and three other independent members including a clinical trialist a statistician, a Patient and Public Involvement (PPI) representative and the CI. The Data Monitoring Committee (DMC) monitors patient safety and trial data efficacy and consists of an independent chair, three other independent members and the CI.

All serious adverse events (SAE’S) are recorded and notified as appropriate to the relevant authorities.

### PPI

A comprehensive programme of PPI engagement was conducted during the set-up stage to inform the development of the symptom-diary data collection, of the parent- and child-facing trial documentation. PPI contributors attend both the Trial Management Group (TMG) and Trial Steering Committee (TSC) meetings, providing ongoing guidance. PPI members will help identify non-academic dissemination avenues, and will advise on materials for press releases, print media, social media and parent-facing materials, including presentation of results using a parent/child-friendly animation.

### Data management and confidentiality

Study data is collected and stored using the TRANSFoRm [19] GCP-validated clinical trial platform that is integrated into the GP’s EHR system. Once a patient presents to the GP with one of the specified otitis media disease codes, eligibility screening is run in the background on their EHR. Should the patient be found suitable for inclusion in the study, the GP is asked to consent the patient/legal guardian. No data is captured in TRANSFoRm until the parent/legal guardian has consented to theirs and their child’s participation. The data is captured through electronic Case Report Forms (eCRFs) completed through the EHR system, and the Patient Reported Outcome Measures (PROMs) completed at set time points by the patient through a web portal on their mobile devices, tablets or desktop computers at home. The data is transmitted using a secure connection and stored inside an encrypted database hosted at King’s College London. A subset of participant information is additionally stored in the REDCap database hosted at the University of Bristol, added by a member of the REST study team.

Both the TRANSFoRm electronic platform and REDCap incorporate data entry and validation rules to reduce data-entry errors and double data entry. Trial staff will ensure that participant anonymity is maintained through protective and secure handling and storage of patient information at the trial centre’s. Data will be anonymised as soon as it is practical to do so in line with the Data Protection Act 1998. Participants’ data is securely held on the databases in line with data protection legislation.

To comply with the Fifth Principle of the Data Protection Act 1998 (this process will be reviewed and updated accordingly with any updates to the guidelines), personal data will not be kept for longer than is required for the purpose for which it has been acquired. Data will be held in compliance with the sponsor’s standard operating procedures.

### Sample size

Our previous trial compared immediate with delayed antibiotic use [1]. Children with AOMd took a median of 3 days (interquartile range (IQR) 2, 4) to achieve the REST primary outcome. Our PPI advised a 1.25-day non-inferiority margin (equivalent to an absolute difference in cure rate of 19.5% at 3 days). A two-group non-inferiority trial normally assumes a 2.5% one-sided Type I error. Using a 1.25% Type I error to detect non-inferiority for two comparisons with 90% power, complete outcome data needed for 106 per arm is 399 with 20% attrition.

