### Statistical analysis

A flow of participants through the trial will be summarised in a Consolidated Standards of Reporting Trials (CONSORT) diagram. Descriptive statistics of baseline clinical and socio-demographic characteristics will be presented to describe the study sample and to ascertain comparability of the randomisation groups.

Data from the internal pilot phase of the study will be assessed against predefined/pre-agreed stop/go criteria to inform the decision as to whether to continue the trial to the ‘main’ phase. The proposed ‘traffic light’ (stop/go) criteria are based on descriptive statistics summarising recruitment, retention and adherence.

The primary analysis will be carried out under the intention-to-treat (ITT) principle, analysing participants as randomised without the imputation of missing data. Kaplan-Meier survival curves will be plotted to depict the probability of symptom resolution over time. Symptom resolution over the 14 days of follow-up will be compared between children allocated to immediate oral antibiotics and those allocated to each of the other treatment groups using a Cox proportional hazards regression model, adjusted for age (stratification variable). The primary outcome will also be analysed using an Accelerated Failure Time (AFT) model, which has previously been recommended for studies of resolution of infectious diseases as previous research has suggested that symptoms of AOM will be resolved in 90% of children by day 8.

The proportion of participants in the immediate topically and delayed orally administered antibiotics arms who achieve symptom resolution within 3 days will be compared (separately) to those in the immediate orally administered antibiotics arm. The absolute difference will be calculated and reported alongside the associated confidence interval, it will then be reported as to whether or not the lower limit of the confidence interval lies within the maximum unimportant difference.

Analysis of secondary outcomes will utilise regression models appropriate for the nature of the outcome measure (i.e. logistic regression for binary outcomes, Poisson or negative binomial regression for count data).

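### The equal 1.25% split across the two non-inferiority comparisons is valid, but a Holm step-down would give more power at the same 2.5% familywise error

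*Protocol article*

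**What the plan says.** The Sample size section starts from the usual level for one comparison: "A two-group non-inferiority trial normally assumes a 2.5% one-sided Type I error". It halves this for the two intervention arms: "Using a 1.25% Type I error to detect non-inferiority for two comparisons with 90% power". The 1.25% is one-sided by context. The resulting size is given as "complete outcome data needed for 106 per arm is 399 with 20% attrition".

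The Statistical analysis section says that the proportions resolved within 3 days in the drops arm and the delayed arm "will be compared (separately) to those in the immediate orally administered antibiotics arm". For that comparison, "The absolute difference will be calculated and reported alongside the associated confidence interval", and the result is read by "whether or not the lower limit of the confidence interval lies within the maximum unimportant difference". The section describes no ordering of the two comparisons, no step-down and no passing of error from one to the other. It gives no confidence level for the interval.

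**The concern.** Dividing the error equally and testing each arm separately is the plain Bonferroni procedure. It protects the familywise error, but it leaves the unspent share unused. Once one arm has been shown non-inferior at 1.25%, the other can be tested at the full 2.5% without the familywise error passing 2.5%. That is Holm's procedure. It declares success wherever Bonferroni does, and in some further cases.

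The trial wants an answer on drops and an answer on delayed prescribing, so the chance of a positive answer on both is a relevant measure of the design. Under the equal split that chance is noticeably below the 90% quoted per comparison, and part of the shortfall can be recovered by wording alone.

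**Working it through.** **The plan's own figures.** Error: 2.5% / 2 = 1.25%, as stated. Attrition: 106 / 0.8 = 132.5, so 133 per arm, and 3 × 133 = 399, as stated. The 106 itself does not follow from the stated inputs. With n = 2p(1 − p)(z₀.₉₈₇₅ + z₀.₉₀)² / 0.195², a day-3 cure rate of 50% (from the median of 3 days) gives 0.5 × 3.523² / 0.038025 = 163.2, so 164 per arm; 75% gives 123; about 80% is needed for 105. That is a separate matter. The main calculation takes the stated 90% per comparison as given, and a lower power is tried at the end.

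**Inputs.**
- One-sided levels 1.25% and 2.5%, with critical values c₁ = 2.241 and c₂ = 1.960.
- Power of 90% per comparison at 1.25%, so each test statistic has mean 2.241 + 1.282 = 3.523 when the arm is truly non-inferior.
- Correlation of 0.5 between the two statistics. This is an assumption that follows from the shared control arm and the equal arms implied by a single per-arm figure.

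**Power, both arms truly non-inferior** (bivariate normal probabilities):
- Bonferroni, both succeed: P(Z₁ > c₁, Z₂ > c₁) = 0.832.
- Holm, both succeed: both must exceed c₂ and at least one must exceed c₁. P(both > c₂) − P(both between c₂ and c₁) = 0.8973 − 0.0038 = 0.894.
- Holm, one given comparison: P(Z₁ > c₁) + P(c₂ < Z₁ ≤ c₁, Z₂ > c₁) = 0.900 + 0.031 = 0.931.
- At least one success, either procedure: 1 − P(both ≤ c₁) = 0.968. It is unchanged because Holm's first step is the Bonferroni test.

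**Familywise error (one-sided).**
- Both arms at the margin: 2.32% under either procedure.
- One arm at the margin, the other clearly non-inferior: 1.25% under Bonferroni, 2.5% under Holm. This is the unused error that Holm spends, and it stays within the bound.

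**Where there is no gain.** If the other arm sits at the margin, power for the first arm is 90.0% under both procedures.

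**Sensitivity to lower power.**

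| Power per comparison, Bonferroni | Same, Holm | Both arms, Bonferroni | Both arms, Holm |
|---|---|---|---|
| 90.0% | 93.1% | 83.2% | 89.4% |
| 80.0% | 84.6% | 68.7% | 77.8% |
| 72.5% (106 per arm, day-3 cure rate 50%) | 77.7% | 58.8% | 69.1% |

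Over this range the gain grows as power falls.

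**The case against.** The strongest reply is that Bonferroni is a valid choice with a practical merit: one fixed-level interval per arm that always agrees with the decision. Under Holm the second arm's level depends on the first arm's result, and an arm could be declared non-inferior while its reported 97.5% interval crosses the margin. This stands as a real, though small, cost. Calling the step-down free would be too strong.

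It can also be said that the sample-size paragraph only sizes the trial, and that sizing at 1.25% fits a Holm analysis, whose first step is 1.25%. A reader might infer that the plan holds the second comparison at 1.25% even after the first has succeeded. The article does not say so. It describes separate comparisons and no step-down, so plain Bonferroni is the natural reading but not an explicit rule.

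A reader might also infer that error control is lost because the deciding interval has no stated level. If 95% intervals decided both arms, the one-sided familywise error would be 4.5% with both at the margin. Nothing in the article says that they will. A 1.25% one-sided test implies a 97.5% two-sided interval, and a condensed article may leave the level to the analysis plan. The missing level is therefore not a finding.

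Finally, the gain needs both arms to be truly non-inferior, and the article's background gives reason to doubt this: drops may not reach the middle ear, and immediate oral antibiotics are said to have strong evidence of benefit. The article also reports 22 children recruited against 399 planned, a number at which the choice of procedure would matter little. Both remarks limit the practical value. Neither makes Holm worse than the equal split.

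**Conclusion.** The point holds as a cheap improvement to a valid procedure. At the stated 90% per comparison, Holm adds about 6 percentage points to the power to show both arms non-inferior (83% to 89%) and about 3 per comparison (90% to 93%). It does so within the same 2.5% one-sided familywise error and with no more children. The figures assume equal arms sharing one control (correlation 0.5), normal test statistics and two truly non-inferior arms. The chance of at least one success does not move from 97%, and an arm gains nothing if the other never succeeds. The documents do not support saying that the plan's error control is wrong or has been abandoned.

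**What to change.** In the Statistical analysis section, state the testing rule for the two comparisons with immediate oral antibiotics:

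1. Take the comparison with the stronger evidence against the margin (the smaller one-sided p-value) and judge it by a 97.5% two-sided interval, which is 1.25% one-sided.
2. Only if it succeeds, judge the other by a 95% two-sided interval, which is 2.5% one-sided. If it fails, declare neither arm non-inferior.
3. Report 97.5% intervals for both arms as well, and say in advance that the second arm's decision may rest on the 95% interval.

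The cost is one paragraph and no patients. The downside is that the second arm's decision interval has a different level and may not match its reported 97.5% interval. If the sponsor values a single fixed-level interval per arm more than the added power, keeping Bonferroni is defensible.

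### With 106 complete children per arm, the day-3 comparison has about 73–85% power on the stated median and IQR, not the 90% given in the Sample size section

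*Protocol article*

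**What the plan says.** The Sample size section starts from an earlier trial: "Children with AOMd took a median of 3 days (interquartile range (IQR) 2, 4) to achieve the REST primary outcome". It then sets a "1.25-day non-inferiority margin (equivalent to an absolute difference in cure rate of 19.5% at 3 days". On error rates it notes that "A two-group non-inferiority trial normally assumes a 2.5% one-sided Type I error", and continues "Using a 1.25% Type I error to detect non-inferiority for two comparisons with 90% power". The result is "complete outcome data needed for 106 per arm is 399 with 20% attrition". It gives neither a day-3 control rate nor a formula.

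The Statistical analysis section makes a Cox model over 14 days, adjusted for age, the primary analysis, and adds an accelerated failure time model. No margin is given as a hazard ratio or a time ratio. A separate paragraph covers day 3: "The proportion of participants in the immediate topically and delayed orally administered antibiotics arms who achieve symptom resolution within 3 days will be compared" with the immediate oral arm, separately for each intervention. The lower confidence limit for the absolute difference is then judged against the largest difference regarded as unimportant. This is the only place in the article where an estimate is tested against a margin, and 19.5 points is the only margin stated on that scale.

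**The concern.** The 90% and the 106 stand beside a margin in percentage points, and the one described non-inferiority test is in percentage points. A reader will take the 90% to apply to that test. The sample size for such a test depends on the control proportion, and the quartiles quoted in the same paragraph limit that proportion. If no proportion within those limits gives 106, the stated inputs and the stated result disagree.

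What is at stake is the chance of missing true non-inferiority on the day-3 comparison. It would be 15% to 27.5% per comparison rather than 10%. Anyone reusing the calculation for a later trial would carry the shortfall forward.

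**Working it through.** **Inputs**
- From the Sample size section: one-sided error 1.25% per comparison (z = 2.2414), power 90% (z = 1.2816), margin 0.195, 106 complete children per arm, 20% attrition.
- Inferred: the day-3 control proportion p. With daily ratings, a median of 3 days means at least 50% resolved by day 3. An upper quartile of 4 days means at most about 75% resolved by day 3.
- Assumed: true difference zero, and a confidence level matching the 1.25% error.

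**Attrition step.** 106 / 0.8 = 132.5, rounded up to 133; 133 × 3 = 399. This reproduces, so the question is only where 106 comes from.

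**Sample size for the day-3 difference**

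n per arm = (2.2414 + 1.2816)² × 2p(1 − p) / 0.195² = 12.41 × 2p(1 − p) / 0.038025

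**Power at 106 per arm**

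Power = Φ(0.195 / √(2p(1 − p)/106) − 2.2414)

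| p at day 3 | n per arm for 90% | Power at 106 |
|---|---|---|
| 0.50 | 163.2 → 164 | 72.5% |
| 0.625 | 153 | 75.5% |
| 0.70 | 137.1 → 138 | 80.4% |
| 0.75 | 122.4 → 123 | 85.0% |
| 0.796 | 106.0 | 90% |
| 0.80 | 104.4 → 105 | 90.5% |

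Simulating the confidence-interval test gives 73.2%, 75.3% and 85.0% at p = 0.50, 0.625 and 0.75. A restricted-null variance moves the range only to 74–86%. A 2.5% error would need 139 per arm at p = 0.50 and 104 at p = 0.75, but the article states 1.25%.

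The formula returns 106 only near p = 0.80. If 80% were resolved by day 3, the upper quartile would be 3 days or less, not 4.

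**Time scale, as a check on how far the point reaches**
- Log-rank comparison of medians 3 and 4.25, with events per arm = 2 × 12.41 / (ln HR)². Exponential times: HR = 3/4.25 = 0.706, about 205 per arm. Weibull fitted to the quartiles (shape 2.27): HR = 0.454, about 40 per arm. These two results bracket 106.
- Difference in mean days with margin 1.25: n = 2 × 12.41 × (SD/1.25)². This gives 106 when SD is about 2.58, and 35 when SD is 1.48, the value a normal IQR of 2 to 4 implies.
- Cox model with 212 children and 90–100% events. If 19.5 points at day 3 is turned into a hazard ratio, ln(1 − p + 0.195)/ln(1 − p), the result is 0.525 at p = 0.50 and 0.584 at p = 0.75, and power is about 93–99%. With HR 0.706 it is about 57–62%.

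So 106 on the time scale is neither confirmed nor refuted; it depends on a distribution and margin that the article does not give.

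**The case against.** The strongest reply is that the 90% was never meant for the day-3 test. The margin is given first as 1.25 days, the 19.5 points appear only in brackets, no two-proportion formula is claimed, and the Cox model is primary. This stands in part. A reader might infer from the table that the trial is underpowered for its primary analysis, or that 106 cannot be obtained on the time scale. The article supports neither inference: the Cox analysis could exceed 90% or fall well short according to the hazard ratio taken as the margin, and plausible time-scale models fall on both sides of 106. The reply does not remove the conflict for the day-3 comparison, which is the only one tested against a margin.

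A second reply is that the quartiles are not attributed to an arm. The earlier trial compared immediate with delayed antibiotics. If the arms were pooled, an immediate-arm rate near 80% is possible; for example, 80% and 60% average 70%. This lowers confidence, because the control rate is inferred. But the article gives no such split, and the pooled quartiles are the only distribution it reports.

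A third is that an article condenses the full protocol, where the method may be set out. That is fair for the missing formula, and its absence is not the complaint. The complaint is that the figures printed together do not agree for the test described.

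Finally, one could quote the joint chance of success on both comparisons. The article does not clearly claim joint power, so no such figure is used here.

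**Conclusion.** The point holds for the day-3 difference in proportions and no further. At a one-sided 1.25% error and a 19.5-point margin, 106 complete children per arm gives about 73–85% power per comparison, against 90% stated; 90% would need 123 to 164 per arm. This rests on a day-3 control rate of 50–75% inferred from the median and IQR, a true difference of zero, and 19.5 points being the margin for that comparison. It would fail if the intended control rate was about 80%, but the article does not state that rate and its quoted upper quartile speaks against it.

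The finding is a misstated or misattributed power figure, not a demonstrated defect of the primary Cox analysis. The Trial status section reports recruitment closed with 22 children, so the correction concerns the published design claim and its reuse rather than trial conduct. It is worth making because it is cheap.

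**What to change.** Correct the Sample size section in one of two ways, chosen by what the calculation behind the 106 actually used.

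1. If it was meant for the day-3 comparison: state the assumed control rate and formula, and restate the power with 106 complete children per arm as about 73–85% for control rates of 50–75%.
2. If the 90% refers to the time scale: say so, give the assumed distribution (with its SD or shape) and the margin on that scale (days, time ratio or hazard ratio), and base the non-inferiority conclusion on that analysis, with the day-3 comparison as supportive. The 19.5-point equivalence should then be shown from the same distribution. For medians 3 and 4.25, the models tried put the day-3 gap at 11 points (exponential), 23 (Weibull fitted to the quartiles), 25 (log-normal) or 30 (normal).

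The first costs one rewritten paragraph. The second also needs a matching sentence in the Statistical analysis section. No extra patients are asked for. The downside is a less favourable stated power for the day-3 comparison.
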